### Sample size

We performed a simulation study to determine the total sample size required to derive precise estimates of effect sizes for a two-arm randomized trial using a 1:1 randomization scheme for the primary intervention (yoga) and the educational film program; estimates were based on regression models using multiple simulations and scenarios, and specifically accounting for heterogeneity of effects. We considered seven combinations of effect sizes at 23 different sample sizes for total of 161 effect and sample size combinations. For each combination we ran 5000 simulations for a total of 805,500 simulations. The seven effect-size combinations were structured under the conservative assumption that all interventions would lead to a small to moderate improvement in outcomes and that the yoga intervention would lead to an improvement equal to or greater than the comparator condition. We used repeated simulations to determine the required post-attrition total sample size needed to obtain precise estimates of all three treatment effects under an intent-to-treat (ITT) analysis of variance (ANOVA) analysis. Based on findings of the simulation study and assuming 20% attrition, a sample size of 44 participants will permit reasonably precise estimates (within 95% confidence intervals of the true effect size value) for the two interventions, as well as reasonable estimates of recruitment, randomization, and adherence rates; moreover, estimates remain robust even at 30% attrition. Thus, the study will be adequately powered even if effect sizes for the yoga program are substantially smaller, and attrition rates greater than observed in our pilot studies [15, 66].

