#### Randomization

Randomization will occur immediately following completion of baseline evaluations and no more than 30 days prior to initiation of the intervention. Eligible participants will be randomized using a 1:1 ratio, to the yoga (*N* = 22) or educational film group (*N* = 22), based on an allocation sequence generated by the study statistician using a randomly varying block randomization method to ensure equal distribution among treatment groups [107].

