*Treatment effect sizes* (*A.2.2*), based on between-group differences in change over time, will be estimated using one-way ANOVA models. Effect size estimates will be calculated using both ITT (primary) and per-protocol analyses. These unbiased estimates of intervention effect size will inform sample size determination for our planned future efficacy trial [147]. Scores on *the Yoga-dosing Questionnaire* (*A.2.3*) will also be assessed using descriptive statistics to determine optimal scheduling and maximum acceptable dosing of yoga for our future trial.

*Missing data*: every effort will be made to minimize missing data relevant to all aims. If missing data does occur and the missing-data pattern (probability model) is not missing completely at random (MCAR), then we will consider approaches appropriate for missing at random (MAR) and missing not at random (MNAR). If the pattern or structure of the plausible missing data suggests MAR, either the EM algorithm [148], inverse weighting [149], or multiple imputation (MI) [150, 151] will be used and the missing-data mechanism will be constructed from the collected data [150, 152, 153]. The selected method will reflect the appropriateness of the method to best estimate the underlying missing-data mechanism [148–150, 152]. Participant characteristics will be assessed, including demographic and lifestyle characteristics, RLS severity, medical history, health-related factors, and baseline questionnaire scores for the estimation of plausible models (i.e., MCAR, MAR, and MNAR) for the missing-data mechanism. While we will not be able to definitively test if the missing data are MNAR, If there are indicators suggestive of MNAR (e.g., drop-outs differ significantly from non-drop-outs in key characteristics), we will use MI in conjunction with a sensitivity analysis to provide a set of plausible conclusions recognizing that each conclusion will be predicated on the assumptions necessary for constructing a MNAR missing-data mechanism model [150, 153].

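### The only named trigger for the MNAR sensitivity analysis is a difference on observed characteristics, which bears on MCAR versus MAR, so whether the analysis runs has little to do with whether it is needed

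*Protocol article*

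**What the plan says.** The missing-data paragraph under Statistical methods works in branches. If missingness is judged not to be MCAR, methods for MAR and MNAR are considered.

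- **MAR branch:** "If the pattern or structure of the plausible missing data suggests MAR, either the EM algorithm", with inverse weighting and multiple imputation (MI) as alternatives.
- **Evidence for judging the mechanism:** "Participant characteristics will be assessed, including demographic and lifestyle characteristics, RLS severity, medical history, health-related factors, and baseline questionnaire scores". All of these are observed participant features.
- **MNAR branch:** it opens with an admission, "While we will not be able to definitively test if the missing data are MNAR", and then gives the rule: "If there are indicators suggestive of MNAR (e.g., drop-outs differ significantly from non-drop-outs in key characteristics), we will use MI". That imputation is to be paired with a sensitivity analysis yielding several conclusions, each resting on its own MNAR assumptions.

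The drop-out versus non-drop-out difference is given as an example, but no other indicator is named. The number of characteristics and the significance level are not stated.

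The same section describes the resulting effect sizes as unbiased and says they will inform the sample size of the planned efficacy trial.

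**The concern.** Under MAR, drop-out depends on things that were measured. Drop-outs and completers then differ on those things, and MAR methods that condition on them remove the bias. Under MNAR, drop-out depends on the unseen week-12 value even after conditioning on what was measured. A comparison of observed characteristics can speak against MCAR, but it cannot separate MAR from MNAR. The named indicator therefore points at the wrong mechanism, and it sits badly with the admission in the same sentence that MNAR cannot be tested.

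The issue is practical here. Participants know their assignment (Blinding) and the symptom outcomes are self-reported (Data collection and outcomes), so yoga participants who feel no benefit may plausibly leave. If they resemble completers at baseline, the named indicator stays quiet except by chance, and a flattering effect size could pass into the planning of the next trial with no check on it.

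**Working it through.** The protocol gives no figure for this rule, so there is none to reproduce. The check asks how the named indicator behaves at the trial's own size.

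**Inputs from the protocol.** Sample size section: "assuming 20% attrition, a sample size of 44 participants will permit reasonably precise estimates", and "estimates remain robust even at 30% attrition". Randomization section: "Eligible participants will be randomized using a 1:1 ratio". Hence 44 × 0.20 = 8.8, about 9 drop-outs against 35 completers; and 44 × 0.30 = 13.2, about 13 against 31.

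**Assumptions not in the protocol.** Two-sided 5% t-tests; baseline to week-12 correlation 0.5; true yoga effect 0.5 SD; drop-out log-odds slopes of 1.0 and 1.5 per SD; other characteristics correlated 0.3 with baseline severity; 1, 7 or 14 characteristics tested.

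**Step 1: power of one comparison.** Non-central t with ncp = d × √(m·c/(m+c)) and m + c − 2 = 42 degrees of freedom.
- 9 vs 35, d = 0.5: ncp = 0.5 × √(315/44) = 1.34, power 26%. At d = 0.8, 55%.
- 13 vs 31, d = 0.5: ncp = 0.5 × √(403/44) = 1.51, power 32%. At d = 0.8, 66%.

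Even as a test against MCAR the indicator is weak.

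**Step 2: chance firing.** With k independent characteristics, none related to drop-out, P(at least one significant) = 1 − 0.95^k: 5% for k = 1, 30% for k = 7, 51% for k = 14.

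**Step 3: simulation**, 4,000 trials per scenario. Baseline Y0 ~ N(0,1); week 12 Y1 = 0.5·Y0 + √0.75·e − 0.5·yoga, higher meaning worse. The drop-out models, each set to average 20%, are:
- MCAR: constant probability.
- MAR: logit P = a + b·Y0.
- Yoga-only MNAR: logit P = a + b·Y1 in yoga, random in film.

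| Drop-out mechanism | 1 tested | 7 tested | 14 tested |
|---|---|---|---|
| MCAR | 5% | 29% | 49% |
| Yoga-only MNAR, b = 1.0 to 1.5 | 9–11% | 32–34% | 51–53% |
| MAR on baseline, b = 1.0 to 1.5 | 65–90% | 75–92% | 84–95% |

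Repeat runs move these by one or two percentage points. When drop-out depends only on the part of the week-12 score that baseline does not predict, the rates are about 5%, 29–30% and 49–50%, the same as under MCAR. The small excess in the yoga-only row arises because the week-12 score is correlated with baseline.

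**Step 4: bias of the planned estimator.** The protocol bases effect sizes on between-group differences in change. In the yoga-only MNAR scenario the completers' change-score difference overstates yoga by about 0.09 SD (b = 1.0) to 0.12 SD (b = 1.5). Under MAR on baseline the baseline-adjusted estimate has bias of about 0.

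**Step 5: meaning for the next trial.** Required sample size varies as 1/effect². With a true effect of 0.5 SD, planning on 0.59 or 0.62 gives (0.5/0.59)² = 0.72 or (0.5/0.62)² = 0.65 of the number needed.

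**The case against.** **The difference is only an example.** A reader might infer that the sensitivity analysis runs only if drop-outs differ from completers. The text does not say so: the difference is introduced by e.g., and the plan collects other information that could point to outcome-related drop-out. Examples are a program evaluation completed on leaving the study, and reasons for non-adherence asked by instructors. This stands. However, the missing-data paragraph does not name any of these as an indicator, and the one it does name is of the wrong kind.

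**Usually skipped is too strong.** A reader might also infer that the analysis is mostly omitted when it matters. That depends on how many characteristics are tested. It is so for one or seven, but at about fourteen the trigger fires about half the time. Those extra firings are chance, at nearly the same rate under MCAR, so they do not rescue the rule.

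**The bias is modest and scenario-bound.** The change-score estimate has a sampling SD of about 0.34, so 0.09–0.12 SD is roughly a quarter to a third of one standard error. If both arms drop out by the same outcome-dependent mechanism, the bias is about 0, and the single test then fires in 21–31% of trials. A baseline-adjusted analysis shows a larger bias in the yoga-only scenario (about 0.13–0.17 SD), but that is not the planned estimator. All this stands and limits the size of the point.

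**The trigger is not the only obstacle.** The ITT set requires a post-randomization assessment, and exploratory outcomes are measured only at baseline and week 12. On the natural reading, participants without week 12 leave the set whatever the trigger does. This stands too, and the fix must address it.

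**An SAP may hold the detail.** Shift sizes and similar choices belong there. The rule itself, though, is stated in the protocol and is mistaken as stated.

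**Conclusion.** The point holds in a limited form. The only indicator named for the MNAR sensitivity analysis bears on MCAR versus MAR, so the decision to run it is largely unrelated to the need for it. Outcome-dependent drop-out in yoga raises the firing rate by only a few percentage points over MCAR, while MAR on baseline, which needs no MNAR step, raises it most.

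The logical part rests on the wording alone. The firing rates and the 0.09–0.12 SD rest on the assumed correlation, slopes, effect and yoga-only mechanism, and they illustrate rather than predict.

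The reach is the exploratory effect sizes of Aim 2.2. A reader might infer that the feasibility conclusions are also at risk; they are not, because recruitment, retention and adherence do not depend on this rule. The change is worth making because these effect sizes are intended to size the efficacy trial.

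**What to change.** Make three changes to the missing-data text:

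1. **Remove the trigger.** Pre-specify an MNAR sensitivity analysis, for example delta-adjusted MI, whenever any week-12 IRLS score is missing, whatever the comparison of drop-outs and completers shows.
2. **Include all randomized participants in it.** State that this differs from the ITT definition for the secondary aims, which would otherwise exclude drop-outs with no week-12 assessment. Baseline data are collected before randomization, so the imputation model has something to work from.
3. **Give the observed differences their proper use.** Say that differences between drop-outs and completers guide the choice of covariates for the MAR model, and nothing more.

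The size and direction of the shifts, and whether they apply to one arm or both, can be set in the SAP before the data are unblinded.

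The cost is two or three sentences of wording and a few lines of MI code. No new data are needed and the sample size does not change.

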### Data monitoring, harms, and auditing

The frequency of data review for this study differs according to the type of data and can be summarized as follows: data on accrual, status of all enrolled subjects, adherence, and AEs will be reviewed by the PI and study coordinator every 4 months; accrual and AEs will also be reviewed yearly by the PI, IRB, Independent Monitoring Committee (IMC) (comprising three experts with appropriate expertise and experience in clinical trials, biostatistics, and clinical medicine), and NCCIH; SAEs will be reviewed per occurrence by all.

While both programs are minimal risk interventions, we are further ensuring participant safety by: using highly trained *Iyengar* instructors experienced in teaching adults with chronic health conditions and in adapting poses to minimize discomfort and risk of injury; including only gentle postures in the program; and maintaining small class sizes to ensure adequate personalized attention. In addition, all participants will be encouraged to report any AEs to study staff and on their yoga and co-intervention logs. Yoga group participants will also be queried about AEs by the yoga instructors during class. Yoga instructors will notify the study coordinator regarding any AE.

The study coordinator will promptly report AEs to the IRB according to protocol and IRB policies; complete an adverse events form and grade the AE; and contact the participant by telephone on a weekly basis to monitor the event until the event resolves, the study is completed, or the participant is removed from the study. In addition, subjects can choose to stop the study at any time. Any serious and unexpected AEs will require re-evaluation of the risk of the study. Monitoring and aggregate review will be performed by the PI, IRB, and IMC through annual review.

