### Interventions

#### Yoga program (active intervention)

Participants randomized to the yoga group will complete a gentle *Iyengar* yoga program based on that developed and successfully implemented in our pilot studies [15, 66]. The yoga program was finalized following detailed review and input from an *Iyengar* Master Trainer.

Program logistics: yoga group participants will attend two 75-min classes per week for the first 4 weeks, then one 75-min class for the remaining 8 weeks, and will be asked to complete a 30-min homework routine 5 days/week on non-class days. Yoga classes will be held at two yoga studios in close proximity to the WVU Health Sciences Center campus (WVU site) and OSU Center for Integrative Health and Wellness (OSU site), respectively. As in our previous trials [15, 66], each yoga class will begin with simple yogic centering and breathing exercises, followed by a sequence of active and restorative poses, and ending with a 10-min guided supine relaxation practice. The yoga routines, including a collective total of 25 common *asanas*, have been tailored for sedentary adults naïve to yoga, gradually increasing in difficulty as students progress. Pose modifications and props (e.g., chairs, blankets, and straps) will be used as needed to enable participants to perform the poses safely and easily, regardless of their level of physical ability or fitness. In addition, each class will be restricted to no more than 12 participants to allow for personalized attention. The home practice (see Table 1) will be performed with the aid of a yoga DVD and a comprehensive, indexed training manual illustrating the homework routines; These guides are based on materials developed for our preliminary trials and modified to reflect the extension to a 12-week intervention period for the proposed study. Participants will also be provided yoga mats and straps to facilitate home practice.

**Table 1 Tab1:** Yoga home practice routines

Home Practice 1: Weeks 1–3 (*use wall for side-angle standing poses*)	
1. Upward extended-leg pose	*Urdhva Prasarita Padasana*
2. Straight-leg pose: (a) bent knee 3x, (b) straight leg 2x	*Supta Padangusthasana*
3. Upward extended arms in mountain pose: (a) palms forward, (b) palms facing	*Urdhva Hastasana in Tadasana*
4. Extended side-angle pose	*Utthita Parsvakonasana*
5. Half-intense pose: (a) hands to wall, (b) hands on chair	*Ardha Uttanasana*
6. Extended triangle pose	*Utthita Trikonasana*

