#### Educational film program (comparator)

Participants assigned to this group will attend one 75 min class per week for 12 weeks, and will be asked to complete a daily log at home recording any RLS or sleep treatments they tried based on what they learned in class or for any other reason. At the first class, film group participants will receive a comprehensive set of lay educational materials regarding RLS symptoms, causes, and epidemiology and detailing nonpharmacologic strategies for RLS management based on current national guidelines, including recommendations regarding sleep hygiene, lifestyle modifications, and behavioral approaches. Each class will be held at the WVU Health Sciences Center, and include a brief meet-and-greet period at the start of class, an instructional film segment of approximately 60 min, and a 10–15-min group discussion, facilitated by a health educator familiar with sleep disorders and common nonpharmacologic treatments. While sitting for 75 min/week is unlikely to lead to worsening of symptoms in this largely sedentary population, we will, as in our previous trials, encourage participants to stand and/or stretch during the film and discussion if they so desire. All participant comments will be noted, and, together with information provided on the exit questionnaire, will be used to refine the program for the larger trial. Upon study completion, film group participants will receive all yoga homework materials, and be offered a half-day workshop in yoga for RLS.

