### Instructors

All study yoga instructors have been certified in *Iyengar* yoga (≥ 500 h), with at least 3 years of experience teaching adults with a range of chronic health conditions and trained in the final RLS yoga protocol by lead study yoga teacher, [name]. Instruction will be aided by an illustrated training manual and reference guide based on our pilot work and provided to each instructor along with the home-practice DVD.

The film intervention will be administered by a health educator versant in sleep disorders and an advanced graduate student trained for this purpose. This program, based predominantly on educational films, is designed to be easily replicable. The instructor’s role is primarily to facilitate group discussion of the content presented in the films.

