#### Stopping rules

This study will be stopped prior to its completion if: (1) the intervention is associated with adverse effects that call into question the safety of the intervention; (2) any new information becomes available during the trial that necessitates stopping the trial; or (3) other situations occur that might warrant stopping the trial. Because this RCT is specifically designed to be a feasibility study, and we will be investigating recruitment rates and optimal recruitment strategies as part of our primary aim, slow accrual would not comprise a justification for stopping the trial.

In addition, the study may be discontinued at any time by the IRB, NCCIH, the OHRP, or other government agencies as part of their duties to ensure that research participants are protected.

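### Adverse events are actively asked about in class only in the yoga arm, so minor film-arm events are likely to be under-recorded and a descriptive comparison by arm would lean against yoga

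*Protocol article*

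**What the plan says.** Under Data monitoring, harms, and auditing, the protocol article first sets a route common to both arms: "all participants will be encouraged to report any AEs to study staff and on their yoga and co-intervention logs". It then adds a second route for one arm: "Yoga group participants will also be queried about AEs by the yoga instructors during class". The sentence after that gives a forwarding duty, again for one arm: "Yoga instructors will notify the study coordinator regarding any AE". Once an AE is known, the coordinator grades it and telephones the participant weekly until it resolves, the study ends or the participant is removed.

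No equivalent query or duty is stated for film classes. The Instructors section describes the film role this way: "The instructor’s role is primarily to facilitate group discussion of the content presented in the films". The comparator section has comments in film classes noted, but for refining the program. The Blinding section has instructors in both arms record attendance, collect logs and contact participants, without mentioning AEs.

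Harms enter decisions in two places. Stopping rules lists as a ground that "the intervention is associated with adverse effects that call into question the safety of the intervention". The Blinding section has three related serious AEs in either group reported to the principal investigator, who may then break the blind.

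**The concern.** An arm that is asked about AEs will usually record more of them than an arm that is only invited to report. Here the difference is written into the design: the article describes AE collection for everyone and then strengthens it for one arm. A table of AEs by arm would therefore mix true differences with differences in how hard anyone looked.

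Two things are at stake. The first is interpretation. The film arm is the natural reference for the background rate of aches, poor nights and passing symptom flares, and that background would be measured less intensively. The second is care of film participants. Because grading and weekly telephone follow-up start only when an event is known, unequal detection also means unequal follow-up. Film-arm events are not far-fetched. The comparator section considers one itself ("While sitting for 75 min/week is unlikely to lead to worsening of symptoms") and expects participants to try RLS or sleep treatments at home.

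**Working it through.** The article states no AE rate, detection rate or harms precision, so there is no figure to reproduce. What can be checked is the number of contacts and the direction and possible size of the distortion.

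**1. Class contacts.**
- Yoga: "yoga group participants will attend two 75-min classes per week for the first 4 weeks, then one 75-min class for the remaining 8 weeks". That is 2 × 4 + 1 × 8 = 16 classes. The article says the query takes place in class but gives no frequency, so 16 is the maximum number of query occasions.
- Film: "Participants assigned to this group will attend one 75 min class per week for 12 weeks". That is 12 classes, with 0 query occasions stated.

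**2. Model.** Assume the same true risk in both arms.
- p = true proportion of participants with an AE.
- s = share of these captured by encouraged self-report, the same in both arms.
- q = share of the otherwise missed AEs that the yoga query picks up.

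Recorded risk, film = p × s.
Recorded risk, yoga = p × [s + (1 − s) × q].
Apparent risk ratio (yoga/film) = 1 + (1 − s) × q / s. The true risk p cancels.

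**3. Results.** The values of s and q are assumptions; none comes from the article.

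| s | q | Calculation | Apparent ratio |
|---|---|---|---|
| 0.9 | 0.3 | 1 + 0.1 × 0.3 / 0.9 | 1.03 |
| 0.7 | 0.5 | 1 + 0.3 × 0.5 / 0.7 | 1.21 |
| 0.5 | 0.5 | 1 + 0.5 × 0.5 / 0.5 | 1.50 |
| 0.3 | 0.8 | 1 + 0.7 × 0.8 / 0.3 | 2.87 |

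**4. In participants.** Take p = 0.4 (also assumed), s = q = 0.5 and the planned 22 per arm.
- Film: 22 × 0.4 × 0.5 = 4.4 participants with a recorded AE.
- Yoga: 22 × 0.4 × 0.75 = 6.6.

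The gap of about two participants would come from ascertainment alone.

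**5. Limits.** The distortion disappears only if self-report is complete (s = 1) or the query finds nothing new (q = 0). Otherwise it runs one way, towards more recorded AEs under yoga. Serious AEs are hard to miss, so s should be near 1 for them and the ratio near 1. With the same query at matched times in both arms, the ratio under equal true risk returns to 1.00.

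**The case against.** The strongest reply is that no comparison of harms is planned. AEs appear in neither the primary nor the secondary aims, nor among the outcomes, and Statistical methods specifies no AE rate, ratio or test. That stands: the point concerns any descriptive comparison that is made, together with completeness of film-arm capture.

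Four stronger readings are tempting, and the article does not support them.
- A reader might infer that film participants are left to spontaneous report. They are not. They are encouraged to report, they keep a daily log, and logs are collected weekly. What they lack is an active question.
- A reader might infer that the stopping rule or the unblinding trigger would be biased. Neither compares rates between arms. The trigger counts related serious AEs, which are the events least likely to be missed.
- A reader might infer that the pilot will carry forward a claim that yoga is safer than the film program. The Discussion lists feasibility and acceptability, refinement of the yoga protocol, and effect sizes for RLS outcomes. It calls yoga safe only conditionally, and not relative to film.
- A reader might infer that worsening from sitting would go unseen. Sustained worsening should show on the IRLS at week 12, which is taken in both arms by blinded assessors, and participants may stand or stretch. Only transient worsening, or worsening in people who drop out before that visit, could be missed.

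Two further replies have some force. Closer questioning of people doing physical poses serves participant protection, which is the stated purpose of that paragraph. The distortion is also conservative for a claim that yoga is safe. Both are true, but neither is a reason to omit the question from film classes.

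Finally, an article condenses a fuller protocol, which might contain a film-arm script. But this article does not merely omit detail: it sets out collection for all participants and then adds to it for one arm.

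**Conclusion.** The asymmetry is certain from the text. Minor or transient AEs are likely to be captured, graded and followed up less completely in the film arm, and a descriptive AE table by arm would tend to overstate yoga harms relative to film. How much is unknown. The range of about 1.03 to 2.9 under equal true risk rests wholly on assumed capture shares and shows only that the effect could be negligible or substantial. Serious AEs should be little affected. The primary feasibility aims, the effect-size estimates and the sample size do not depend on this point. It is a modest weakness that is cheap to correct.

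**What to change.** 1. Have the film facilitator ask one scripted AE question once a week in class. In yoga classes, designate one weekly query with the same wording as its match, so that the two-class weeks do not leave an imbalance. Any additional yoga query can stay for safety but should be kept apart in the comparison.
2. Give film facilitators the same duty as yoga instructors to notify the study coordinator.
3. Keep AE recording identical on both arms' logs.
4. If an AE question is asked at the end of the study, the coordinator should ask it, not the blinded assessor, since the answer could reveal the arm.
5. Report AEs by arm and by source (prompted or self-reported).
6. If collection stays unequal, state that AEs will be described within arm only.

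Cost: one question at existing classes and a check of the log form, with no extra staff. More minor events will be recorded in the film arm. The article says the trial is open for enrollment and runs in cohorts, so later cohorts could adopt the change, subject to any approval required under Ethics and dissemination. Events from cohorts before and after the change should then be kept distinguishable.
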